**Study Design:**

A cluster randomized controlled trial will be implemented in the state of Goa, on the west coast of India. Twenty-four primary care facilities, 12 from the government sector and 12 from the private sector, will be enrolled in two consecutive phases. For each sector, facilities will be randomly allocated within strata defined by urban/rural location, population size and presence of a visiting psychiatrist. Facilities will be randomly allocated to receive the collaborative stepped care intervention or the enhanced usual care control intervention. Both arms share two components of the intervention, viz., routine screening, and in the government clinics provision of antidepressants. In addition, the collaborative stepped care arm also provides a range of psychosocial treatments delivered by a specially trained Health Counselor, and supervision by a visiting Psychiatrist. A total of 3600 primary care attenders who are detected to suffer from a CMD based on a validated screening questionnaire will be recruited. The primary outcome is the proportion of subjects who recover from an ICD10 defined CMD at baseline by 6 months. Additional endpoints at 2 and 12 months will assess the speed and sustainability of achieving the primary outcomes. Other outcomes will include recovery from ICD10 defined depression and incidence of ICD-10 among individuals who were sub-threshold cases at baseline. Economic and disability outcomes will be assessed to estimate incremental cost-effectiveness ratios.

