### Selection of facilities/randomisation

The sampling frame for phase 1 consisted of PHCs with minimum space available for the intervention team and which were not involved in preliminary phases related to the intervention development, and which have at least 350 attenders per month. Facilities were stratified into three strata; urban with a visiting psychiatrist (VP), rural with a VP, rural without a VP. Two intervention and two control PHCs were selected at random from each stratum, using on-line software by the MANAS trial statistician (HW) [48]. A given seed number was used to enable the randomization procedure to be reproduced. This guards against misallocation or changes in allocation at a later stage. The sampling frame for phase 2 will consist of all GPs with adequate clinic space and who consent to participate, and will be similarly stratified.

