A key factor in estimation of the sample size for a cluster RCT is the coefficient of variation (SD/mean) of the true proportions with the outcome between clusters within each arm [59]. In the absence of outcome data to estimate k in Goa, we have used the recovery rates of CMD in the two Asian centres (Shanghai, Bangalore) of the WHO multinational study of CMD in general health care [10], and data from 8 studies of CMD prevalence in India (two in urban GPs, three in urban PHCs and three in rural PHCs) [12] all of which estimate k < 0.2. The proposed trial is located in one state of India and facilities are stratified according to their rural/urban location and private/public sector; hence the value of k is likely to be even lower [59,60]. To be conservative, we have used an estimate of k = 0.2.

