### Data management & analyses

Data will be collected using a hand-held computer (Palm-OS), and exported to Stata 9.0 for statistical analysis. Given direct entry of responses, we expect there to be minimal data entry errors. Findings will be reported as per the CONSORT guidelines for cluster randomized controlled trials [62]. Baseline comparability will be assessed for individuals who did not consent to be part of the trial, and of participants who could and could not complete review assessments. Comparability of the two intervention arms will be assessed for a variety of potential confounding factors assessed at 2 months, notably: age, sex, education, per capita income, severity of mental health scores, ICD10 diagnostic distribution, and comorbidity with alcohol use and physical health problems.

The primary analyses will be intention-to-treat, regardless of adherence to the intervention, and will be based on outcomes 6 months after diagnosis. Logistic regression generalized estimating equations with robust standard errors will be used to compare case prevalence in the two arms, allowing for any within-facility clustering resulting from the cluster randomized design [63], and adjusting for baseline mental health score. Further analyses will adjust for any other of the a-priori defined confounding factors list above for which randomization did not achieve balance between the two arms at baseline. These analyses will be carried out for the different patient groups defined in Table 3, with their respective outcomes as described above. For each of these primary outcome analyses, we will present an estimate of the effect size as an odds ratio and 95% confidence intervals, and a coefficient of intracluster correlation. A number of secondary analyses are proposed, which are listed in the Trial Registration protocol.

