### Trial monitoring

The following 'sentinel' outcome data will be recorded upon completion of interviews for monitoring and safety requirements, and reported to the Trial Steering Committee and Data Monitoring & Ethics Committees at least quarterly: number and proportion of completed outcome assessments and refusals; ICD10 case status for any CMD and Depression; hospitalizations; suicide attempt; and deaths.

No stopping rules are proposed because serious adverse events are not expected in the trial since none of the treatments being offered are experimental or associated with serious outcomes. A recent systematic review has shown that RCTs stopped early show implausibly large treatment effects and that there needs to be a balance between the ethical concerns of safeguarding interests of patients who have been randomized in the trial while also "protecting society from overzealous premature claims of treatment benefit [64,65]." Furthermore, the trial will proceed to phase 2 (GP facilities) without conducting formal interim analyses at the end of phase 1 (PHC facilities) since, even if such analyses showed considerable impacts of the intervention, these may not be generalizable from PHC to GP facilities.

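### Facilities are randomised within sector and strata, but the stated primary model has no term for either; add them, and only with a small-sample correction

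*Protocol article*

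**What the plan says.** **Randomisation.** The Abstract (Study Design) says: "For each sector, facilities will be randomly allocated within strata defined by urban/rural location, population size and presence of a visiting psychiatrist". For the public-sector phase, Selection of facilities/randomisation says: "Facilities were stratified into three strata; urban with a visiting psychiatrist (VP), rural with a VP, rural without a VP". It adds: "Two intervention and two control PHCs were selected at random from each stratum". For the private-sector phase it says only that the frame will consist of consenting GPs with adequate space "and will be similarly stratified".

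**Primary model.** Data management & analyses specifies logistic GEE with robust standard errors, "allowing for any within-facility clustering resulting from the cluster randomized design [63], and adjusting for baseline mental health score". Further analyses add factors from a listed set if randomisation left them unbalanced. That set is age, sex, education, income, mental health severity, diagnostic distribution, and alcohol and physical comorbidity. Sector, location and visiting psychiatrist are not in it.

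**Variance assumption.** The sample size section argues: "facilities are stratified according to their rural/urban location and private/public sector; hence the value of k is likely to be even lower". It nevertheless keeps k = 0.2 as a conservative value.

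**The concern.** The article fixes its primary model explicitly, so this is not a detail left to an analysis plan. The model leaves out the factors that restricted the randomisation. The fallback rule cannot repair that, for two reasons: the list holds only individual-level factors, and strata allocated two v two are balanced by design, so an imbalance rule would never select them.

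Stratified allocation balances strata between arms, which makes the estimated effect itself more stable. A standard error that ignores strata still contains the differences between them. If strata predict recovery, that standard error is too large, the interval is too wide and the test rejects too rarely under the null. The authors appear to believe that strata do predict outcome, since they expect stratification to lower k.

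There is also a problem of definition. The Abstract names population size as a stratifier and the phase 1 strata do not use it. Stratum terms cannot be written down until that is settled.

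**Working it through.** **1. Reproduce the stated power.** Inputs from the sample size section: c = 12 facilities per arm, m = 75 definite cases per facility, k = 0.2, 5% level (taken as two-sided).

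V = p0(1-p0)/m + p1(1-p1)/m + k²(p0² + p1²); power = Φ(√[(c-a)(p1-p0)²/V] - 1.96)

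For 65% v 50%: V = 0.00333 + 0.00303 + 0.04 × 0.6725 = 0.03327.
- a = 1 (unstratified form): √(11 × 0.0225/0.03327) - 1.96 = 0.77, power 77.9%.
- a = 2 (matched or stratified form): √(10 × 0.0225/0.03327) - 1.96 = 0.64, power 73.9%. The article states 74%.

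With a = 2 the other stated figures also reproduce: 91.7% for 70% v 50% (stated more than 90%), 94.2% for depression (94%), 99.5% for possible cases (99%) and 68.8% for sub-threshold cases (about 70%). The stated powers are thus consistent with a formula that makes an allowance for stratification.

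**2. Effect on the standard error.** Let r be the share of between-facility variance explained by strata and sector. The article gives no value, so a range is shown. Multiplying the k² term by (1-r), for 65% v 50%:
- r = 0.10: standard error ratio 0.959 (4% smaller)
- r = 0.25: V = 0.00637 + 0.75 × 0.0269 = 0.02654; √(0.02654/0.03327) = 0.893 (11% smaller)
- r = 0.50: V = 0.00637 + 0.50 × 0.0269 = 0.01982; ratio 0.772 (23% smaller)

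**3. Cluster-level simulation.** Six strata of two + two facilities (assumed: three in phase 2 as in phase 1), 75 cases each, k = 0.2, 20,000 runs. Strata ignored: t test on 24 - 2 = 22 degrees of freedom. Strata fitted: 24 - 7 = 17.

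| r | Type I error, ignored v fitted | Power at 65% v 50%, ignored v fitted |
|---|---|---|
| 0 | 4.9% v 4.9% | 78.2% v 77.0% |
| 0.10 | 4.1% v 4.8% | 79.0% v 80.2% |
| 0.25 | 3.2% v 4.8% | 80.4% v 84.7% |
| 0.50 | 2.0% v 5.0% | 83.3% v 93.1% |

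A second set of 40,000 runs per scenario, with a facility SD of 12 percentage points, gave power of 75.6% v 74.5%, 79% v 84% and 82% v 93% at r = 0, 0.25 and 0.50.

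**4. The analysis the article names.** Logistic GEE with uncorrected robust standard errors and a z test, under the null, baseline score not modelled:

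| r | No strata, 8,000 runs | Six strata, 8,000 runs | No strata, 300 runs | Six strata, 300 runs |
|---|---|---|---|---|
| 0 | 6.5% | 10.2% | 8.0% | 12.7% |
| 0.25 | 4.9% | 11.7% | 5.3% | 12.3% |
| 0.50 | 3.0% | 11.1% | 3.0% | 14.7% |

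The 8,000-run set used working independence. The 300-run set used exchangeable correlation and has a Monte Carlo error of about 1-2 points. Adding strata without a correction makes the test clearly anti-conservative.

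**5. Sector on its own.** With c = 6 per arm, power for 70% v 50% is 56% (a = 2) to 66% (a = 1). An arm-by-sector interaction has about 15%, 28% and 45% power for a 10, 15 and 20 point difference in effect.

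**The case against.** **The error is on the safe side and no promise is broken.** This stands. The sample size section takes no credit for a lower k, and every unstratified power at 65% v 50% in step 3 (75.6% to 83.3%) exceeds the stated 74%. Power even rises with r when strata are ignored, because stratified allocation helps by itself. What is forgone is power beyond what was promised.

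**The gain rests on an unknown.** This also stands. At r = 0, fitting strata costs about a point. Adjustment for baseline score, which the simulations omit, may absorb part of any stratum difference.

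**The obvious repair can do harm.** This is the strongest objection. Uncorrected, the stated GEE without strata runs from slightly liberal to conservative as r rises; with six strata it is at about 10-15%. It settles how the change must be made, but does not justify leaving the strata out.

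**Pooling the sectors.** A reader might infer that one pooled odds ratio hides a sector difference that the authors expect. The documents do not support this. Trial monitoring says of phase 1 impacts only that "these may not be generalizable from PHC to GP facilities", as a reason for going on without an interim analysis; it gives no direction or size. Fluoxetine is supplied to PHCs and not to GPs, which makes a difference plausible but does not predict one. Trial objectives and outcomes declares the overall effect in primary care as the aim, so pooling is a legitimate choice. Secondary analyses are referred to the trial registration protocol, which is not shown and may contain sector estimates.

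**Conclusion.** The mismatch between design and analysis is real. Its consequence is conditional and, for a correctly sized test, conservative. At 65% v 50%, fitting strata changes power by about -1 point if strata explain none of the between-facility variance, +4 to 5 points at a quarter and +10 points at a half. The matching type I error with strata ignored is about 5%, 3% and 2%. These figures assume a two-sided 5% level, 75 cases per facility, six strata and the stated values of r. Two v two allocation is stated only for phase 1 and is carried over to phase 2.

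A reader might go further and conclude that the stated power is wrong or the primary test invalid. Neither follows from the missing stratum terms.

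The inconsistency over population size stands separately. It may have been meant for the GP phase, but the article does not say so.

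**What to change.** 1. In the primary model, add sector and the randomisation strata within sector as fixed effects, alongside baseline mental health score.
2. In the same sentence, specify a small-sample correction to the robust standard errors with t-based degrees of freedom, or replace the GEE with a stratified cluster-level analysis. Do not make the first change without this one.
3. Reconcile the stratifiers in the Abstract with those in Selection of facilities/randomisation, and state the phase 2 strata, so that the model terms are defined.
4. Optionally, if the registration protocol does not already provide for it, report PHC and GP effects with 95% confidence intervals as descriptive secondary results. Their power is too low for separate tests.

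The cost is a change of analysis wording, implementation of the correction, and five facility-level degrees of freedom (22 to 17). The last is worth about 1 point of power if the strata explain nothing.

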#### Sample size

##### a) Definite cases

150 participants with a GHQ score >5 will be recruited from each of 24 facilities. Based on the piloting stage experience that up to 25% of these participants will either not be traced by the outcome evaluators or will not consent to participate, and that at least 1 in 3 'cases' identified by the GHQ are Sub-Threshold cases, we anticipate that at least 75 definite cases (see Table 3) from each facility will complete the outcome evaluation at the 6 month end-point. This gives a total sample size of 1800 in which to assess our primary outcome: recovery rate of ICD-10 defined CMD at 6 months among definite cases at baseline. This will have more than 90% power to detect at the 5% level of significance a difference in recovery rates of 70% in the Collaborative Stepped Care versus 50% in the Enhanced usual care control arm. If the recovery rates are 65% and 50% respectively, we will have 74% power to detect a significant difference. Similarly, we have around 90% power to detect a difference in proportion recovered from depression at 6 months of 50% in the Collaborative Stepped Care arm versus 30% in the Enhanced usual care arm.

The assumptions underlying this calculation are as follows. The recovery rates in the Chilean trial [18], whose intervention model is the one being used in this study, showed a gap in recovery at 6 months of 70% versus 30% between the two groups. However, our trial is evaluating effectiveness of introducing this model into routine care, and so we would expect a smaller difference between rates than in an efficacy trial. Furthermore the Chilean trial focused on Depression, while ours will also recruit subjects with less severe CMD who might potentially have higher spontaneous recovery rates in both treatment arms. There are no existing data on the recovery rates of CMD in routine PHC or GP in India. The limited data from other developing countries, including outcomes of Usual Care groups in efficacy trials, suggests that between 30% and 50% of subjects with a CMD recover without active intervention by 6 or 12 months after recruitment [16,18,58]. We therefore based our primary sample size calculation on a likely conservative difference of 20% between the two arms (compared to 40% in the Chile trial), and on recovery rates of 30–50% in the Enhanced usual care control arm.

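### The further adjusted analyses pick their covariates by observed imbalance; a short prognostic list fixed in advance would serve better

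*Protocol article*

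**What the plan says.** All of this is in the Protocol article, Data management & analyses.

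- The primary model: "Logistic regression generalized estimating equations with robust standard errors will be used to compare case prevalence in the two arms", with clustering by facility allowed for, "and adjusting for baseline mental health score". This is a single covariate, fixed in advance.
- The rule at issue: "Further analyses will adjust for any other of the a-priori defined confounding factors list above", limited to those "for which randomization did not achieve balance between the two arms at baseline". No test, threshold or other criterion for balance is given.
- The candidates are age, sex, education, per capita income, severity of mental health scores, ICD-10 diagnostic distribution, and comorbidity with alcohol use and physical health problems. Once the baseline score is in the model, seven remain.
- The analyses are repeated for the different patient groups, and effects are reported as odds ratios.

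**The concern.** The candidates are named in advance, but the data decide which of them enter. Under randomisation any baseline difference is due to chance. What a covariate does for precision depends on whether it predicts recovery, not on whether it differs between arms. The trigger therefore leaves out prognostic factors that happen to balance and brings in non-prognostic ones that happen not to.

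Three things are at stake, all confined to the adjusted analyses:

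- The model cannot be stated before the data are seen.
- Some available precision is discarded.
- The adjusted test drifts from its nominal level.

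There is also a reporting problem. Odds ratios change with the covariates conditioned on, even without confounding. If the trigger picks different covariates in different patient groups, the adjusted odds ratios are not directly comparable across groups.

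**Working it through.** **1. The plan's own power figure, to fix the setting.** Inputs from the Sample size section: 12 facilities per arm, n = 75 definite cases per facility, k = 0.2, 5% level (two-sided assumed). With z_power = √((c − a)/v) − 1.96, v = [p0(1−p0)/n + p1(1−p1)/n + k²(p0² + p1²)]/(p0 − p1)², c = 12, and a = 2 for a stratified design:

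- 70% v 50%: v = (0.00333 + 0.00280 + 0.0296)/0.04 = 0.893; √(10/0.893) − 1.96 = 1.39; power 91.7% (stated: more than 90%).
- 65% v 50%: v = (0.00333 + 0.00303 + 0.0269)/0.0225 = 1.479; √(10/1.479) − 1.96 = 0.64; power 73.9%, in line with "If the recovery rates are 65% and 50% respectively, we will have 74% power to detect a significant difference".

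These figures involve no further covariates, so the rule does not touch them.

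**2. How often chance imbalance would be flagged.** The protocol gives no criterion. Assume a patient-level test at p<0.05. With 75 patients per facility the design effect is 1 + 74 × ICC, and the flag rate is P(|Z| > 1.96/√design effect):

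- covariate ICC 0.02: design effect 2.48, flag rate 21%
- covariate ICC 0.05: design effect 4.70, flag rate 37%

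If the seven factors were independent, the chance of at least one flag would be 1 − 0.79⁷ ≈ 81% to 1 − 0.63⁷ ≈ 96%. A test that respects clustering still gives 1 − 0.95⁷ = 30%.

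**3. One covariate, analysis of 24 facility means.** 40,000 simulated trials per setting, imbalance called at p<0.05, unadjusted power about 80%. R² is the assumed share of between-facility outcome variance that the covariate explains.

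| R² | Power, adjust if unbalanced | Power, always adjust | Type I error, adjust if unbalanced |
|---|---|---|---|
| 0.1 | 80.4% | 82.3% | 4.8% |
| 0.3 | 80.9% | 90.4% | 4.2% |
| 0.5 | 81.6% | 97.0% | 3.8% |

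Always adjusting holds its error at 5.0–5.1%. With a p<0.20 trigger the rule's error is 4.4%, 3.7% and 2.6%.

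The mechanism shows at R² 0.3. The covariate is flagged in 5.1% of null trials, and there the adjusted test rejects 4.6%. In the other 94.9% the unadjusted test rejects 4.2%. Overall: 0.051 × 0.0462 + 0.949 × 0.0417 = 0.042. The rule removes the unlucky trials (where the unadjusted test would have rejected 19.7%) and then keeps an over-wide standard error in the rest.

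**4. One covariate, the protocol's type of model.** Logistic GEE with robust standard errors, independence working correlation, 24 × 75 binary outcomes, baseline score always included, allocation within six strata, facility-level imbalance test at p<0.05, t(22) reference; 4,000 null and 2,500 alternative runs.

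| Covariate log-OR per SD, ICC | Power, adjust if unbalanced | Power, always adjust | Type I error, adjust if unbalanced |
|---|---|---|---|
| 0.5, 0.1 | 84.7% | 88.3% | 5.2% |
| 1.0, 0.1 | 71.5% | 86.3% | 4.2% |
| 1.0, 0.2 | 61.7% | 86.3% | 3.6% |

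Always adjusting has error 5.2–5.6%. The last two rows assume a very strong covariate. With a normal reference, never and always adjusting both run at about 6–7% and the rule at 4.9–6.5%. That excess comes from robust standard errors on 24 clusters and is a separate matter; the rule does not add to it.

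**5. Several covariates.** With three covariates of joint R² 0.1 and 24 facility means, always adjusting gave 77.8% against 78.9% for the rule, so there was no gain. In a patient-level GEE-type simulation (baseline score included, stratified, seven covariates, 1,200 runs per setting), always adjusting was never worse than the rule. The difference ran from none with null or weak covariates to about 2–8 points with moderate or strong ones, with error about 5–6%. Monte Carlo error of a single power estimate near 80% is √(0.8 × 0.2/1200) ≈ 1.2 points.

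**The case against.** **Scope.** The rule governs further analyses. A reader might infer that the trial's main test loses power or has a data-chosen covariate. The text does not support that: the primary model has one fixed covariate and no trigger. The sentences after the rule speak loosely of primary outcome analyses, but they do not bring the trigger into the primary model. This objection stands.

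**Direction.** A reader might infer that data-driven selection inflates false positives. The simulations show the reverse: the shift relative to always adjusting is nil or downwards. This also stands.

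**Assumptions.** The imbalance criterion, the covariate ICC and the prognostic strength left after the baseline score are not in the protocol, and the large power losses come from one strongly prognostic covariate. This stands, and it is why no single figure can be given for the loss.

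**Too many covariates.** With seven covariates in an ANCOVA of 24 facility means, always adjusting can do worse than the rule: 59% v 64% at joint R² 0.1, and ahead only at higher values (70% v 67% at 0.3, 83% v 72% at 0.5). That cost comes from spending facility-level degrees of freedom, and it did not appear in the patient-level simulation above. What survives is a reason to keep the list short.

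**Left to the analysis plan.** A plan not shown could supply a cut-off for imbalance. It could not cure the rule, because any cut-off still selects on imbalance. The protocol states the rule; it does not leave it open.

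**Conclusion.** The point holds as a minor one. The primary analysis and the stated power are untouched. The further adjusted analyses use a poor selection rule. Their content is unknown until the data are seen, they give up precision whenever a prognostic factor happens to balance, and their test is somewhat conservative when the covariates are prognostic.

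The loss against always adjusting runs from about zero with weak covariates to several points or more with strong ones. This range depends on the assumed imbalance criterion, on prognostic strength beyond the baseline score, and on the covariate ICC. The direction does not rest on one trigger: it appeared with facility-level triggers at different cut-offs and, for the error rate, with a patient-level trigger as well.

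**What to change.** Replace the imbalance trigger with a short prognostic set drawn from the listed factors and fixed before any comparison of arms: for example age, sex, education and ICD-10 diagnosis, as measured at baseline, plus the randomisation strata. Include it in the adjusted analysis whatever the observed balance and for every patient group; where a group is defined by its baseline diagnosis, that term drops out if it is constant. Report baseline balance descriptively and do not use it to choose covariates.

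The requirement of baseline measurement should be explicit, because the same section describes "a variety of potential confounding factors assessed at 2 months" yet judges balance at baseline. That inconsistency is separate from the selection rule.

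Cost: a sentence or two, and no new data if these factors are recorded at entry. The small downside is a few extra parameters with 24 clusters, which is the reason not to force in all seven factors.

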### Objectives

The primary objective is to evaluate the impact of the intervention on the proportion of subjects who recover from an ICD10 defined CMD at 6 months follow-up. Secondary objectives include evaluating the impact of the intervention among the sub-group of those who are suffering from a Depressive Episode at baseline, the mean CIS-R score among those who are probable (i.e. screen-positive) cases at baseline, and the prevalence of ICD-10 CMD at 6 months among those who were sub-threshold cases at baseline.

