### Trial objectives and outcomes

It is our objective to study the overall effect of the intervention on the treatment and outcome of CMD in primary care. Four primary research questions are being addressed in the trial, relating to clinical outcomes in different groups of patients, defined according to their type of CMD at baseline (Table 2). From a practical or policy perspective, we need to evaluate the impact on all patients who are identified on the basis of the short screening procedure. Our primary analysis will focus on the subgroup for whom previous evidence is clearest regarding benefit: definite ICD-10 CMD. The outcome will be assessed through home visits at 6 months using the CISR which generates both CMD case and Depression case outcomes based on ICD10 criteria; and a CISR total score. Six months is chosen as the primary endpoint because it marks the maximum duration of the first-line drug and psychological components of the intervention. Other end-points at 2 and 12 months will assess the rate and persistence of clinical recovery. Other outcomes include recovery from Depression, the mean CIS-R score, and prevalence of ICD-10 among sub-threshold cases (Table 2).

In addition, economic costs and outcomes will be measured using the Costs of Illness Schedule, developed for economic analyses of mental disorders in India [9] and used in the previous efficacy trial in Goa [16]. This schedule includes both direct and indirect costs, due to health problems, incurred by the participants, but does not include the direct costs of the intervention itself. The latter will be computed by deriving a monetary value for each component of the intervention based on actual costs, and applying these to each individual based on the process indicators which reflect the actual contact with the intervention. Disability levels will be assessed using the WHO12 item Disability Assessment Schedule, based on the Brief Disability Questionnaire which has been used in Goa [14,57], and input into the estimation of opportunity costs.

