##### d) Depression cases

Our pilot data has shown that only 1/3 of CMD cases are suffering from ICD-10 depression. Thus the proposed sample size would yield about 25 depression cases per facility traced at 6 months, giving a total effective sample size of 600; this has 94% power to detect a difference in recovery rates of 30% in the Enhanced usual care control arm and 50% in the Collaborative Stepped Care arm at 6 months. Again these are conservative estimates compared to the achievements of the Chile trial.

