For the economic analysis, health care costs and other patient- or family-borne costs will be computed and compared at 2, 6 and 12 months, and subsequently related to changes in health outcome: both the primary outcome measure of depression status and also Quality Adjusted Life Years (QALYs). A culturally specific and conceptually solid utility measure for depression – necessary for the estimation of QALYs – will be generated by relating health state valuation scores (taken from an Indian population as part of a wider WHO multi-country study) to summary scores on the WHO-DAS. In the event that dominance is not shown, i.e. the intervention is more effective but the costs are also more than the usual care group, we will estimate the probability of dominance and estimate incremental net benefit and incremental cost-effectiveness ratios. The latter will be computed, together with their confidence intervals (using bootstrapping techniques to overcome expected skewness of cost data). Cost-effectiveness acceptability curves will also be derived in order to show the probability of any cost-effective advantages for the component interventions at a range of 'willingness to pay' threshold levels.

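### The economic analysis names depression status as the primary outcome, but the trial's primary outcome is recovery from any ICD-10 CMD, so the two halves of the hypothesis would rest on different endpoints

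*Protocol article*

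**What the plan says.** Under Data management & analyses, the economic paragraph compares costs at 2, 6 and 12 months and relates them to two effect measures: "both the primary outcome measure of depression status and also Quality Adjusted Life Years (QALYs". QALYs are to come from health state valuations linked to WHO-DAS summary scores, described as a utility measure for depression. Incremental cost-effectiveness ratios and net benefit follow only if dominance is not shown.

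The rest of the article defines the primary outcome differently:

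- Objectives: the primary objective concerns "the proportion of subjects who recover from an ICD10 defined CMD at 6 months follow-up". The subgroup with a depressive episode comes under secondary objectives.
- Trial objectives and outcomes: "Our primary analysis will focus on the subgroup for whom previous evidence is clearest regarding benefit: definite ICD-10 CMD". Depression is placed elsewhere: "Other outcomes include recovery from Depression, the mean CIS-R score, and prevalence of ICD-10 among sub-threshold cases (Table 2".
- Sample size, a) Definite cases: the primary outcome is the "recovery rate of ICD-10 defined CMD at 6 months among definite cases at baseline".
- The Abstract agrees: recovery from CMD is primary, and recovery from depression is among the other outcomes.

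Sample size, d) Depression cases adds that "only 1/3 of CMD cases are suffering from ICD-10 depression".

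**The concern.** CMD status and depression status are not two names for one variable. Trial objectives and outcomes says that the CIS-R yields both, and Trial monitoring reports them separately. An analyst who follows the economic paragraph literally would pick the variable that is not primary.

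Cost-effectiveness is half of the hypothesis under Aims, and the Background says that scale-up may turn on it. If the clinical comparison counts recoveries from any CMD while the economic comparison counts changes in depression status, the two answers do not describe the same benefit. Patients with anxiety or mixed disorder who recover would count in one and not, through this measure, in the other. The paragraph also does not say whose costs go with the depression outcome, and that choice largely decides how the resulting ratio compares with a cost per CMD recovery.

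**Working it through.** **Inputs, all from Sample size**

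- Recruitment: "150 participants with a GHQ score >5 will be recruited from each of 24 facilities", so 24 × 150 = 3600.
- Loss to follow-up up to 25%; at least one third sub-threshold; one third of CMD cases with depression.
- CMD recovery 70% v 50% (20 points), or 65% v 50% (15 points) in the alternative scenario.
- Depression recovery 50% v 30% (20 points).
- New CMD in sub-threshold cases: 5% v 10%.

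**Step 1. Reproduce the plan's counts**

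- Screen-positives followed up: 3600 × 0.75 = 2700.
- Definite cases: 2700 × 2/3 = 1800, as stated.
- Depression cases: 1800 × 1/3 = 600, as stated.

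With equal arms (an assumption for Phase 2) this gives 1350 screen-positives, 900 definite cases and 300 depression cases per arm.

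**Step 2. Extra good outcomes per arm**

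- CMD recoveries in definite cases: 900 × 0.20 = 180, or 900 × 0.15 = 135.
- Depression recoveries: 300 × 0.20 = 60.
- CMD prevalence in all screen-positives: control 0.10 × 1/3 + 0.50 × 2/3 = 36.7%; intervention 0.05 × 1/3 + 0.30 × 2/3 = 21.7%. These match the stated 37% and 22%. (The bracketed working printed for the intervention arm shows 50% where the preceding sentence and the result need 30%.) The difference is 15 points, so 1350 × 0.15 = 202.5 fewer cases.

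**Step 3. Compare the ratios**

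Multiplier = (cost per depression recovery) ÷ (cost per CMD recovery). Where the same incremental cost is used for both, it cancels and the multiplier is CMD gains ÷ depression gains.

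| Costs taken over | CMD effect | Multiplier |
|---|---|---|
| All definite cases | 70% v 50% | 180/60 = 3.0 |
| All definite cases | 65% v 50% | 135/60 = 2.25 |
| All screen-positives | 37% v 22% | 202.5/60 = 3.4 |
| Depression cases only | 70% v 50% | 0.20/0.20 = 1.0 |
| Depression cases only | 65% v 50% | 0.15/0.20 = 0.75 |

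The first three rows assume no difference between arms in new depression among those not depressed at baseline. The last two compare a ratio within depression cases with a CMD ratio within definite cases, and assume equal incremental cost per patient. If depression cases cost r times as much per patient, those two rows are multiplied by r: at equal 20-point effects, r from 0.5 to 3 gives 0.5 to 3.0.

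**Step 4. What the text decides among these rows**

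Nothing firmly. Every screen-positive patient is eligible for the facility's programme, intervention costs are to be applied to each individual, and the economic paragraph restricts nothing to depression cases. That leans towards the first three rows, but the cost population is not stated.

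**The case against.** The strongest reply is that this is a loose label in a condensed article. The words primary outcome measure point back to the trial's endpoint, so readers would understand CMD. Aims names both CMD and Depression, and Trial objectives and outcomes speaks of four primary research questions, one of which concerns depression cases, so a depression outcome is not foreign to the economic question. The plan also expects dominance, includes QALYs, and states that the economic outcome is not powered.

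Part of this stands. Cost per depression recovery is a legitimate secondary analysis. The sample size, clinical analysis and data collection are untouched. The QALY measure rests on WHO-DAS scores, and nothing limits those to depression cases.

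It does not remove the contradiction. The article uses CMD and depression as distinct CIS-R outcomes, so the label selects a different variable. Expected dominance does not help either: dominance itself needs an outcome that improves, and the fallback analyses need an effect measure.

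Two stronger readings are tempting:

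- A reader might infer that the ratio would be three times too high. The article states no ratio and no incremental cost. The factor of 3 needs whole-sample costs set against depression-only recoveries, and a cost per depression recovery is a different quantity, not an inflated cost per CMD recovery.
- A reader might infer that the two thirds without depression can add nothing to the effect side. They can gain QALYs, and the arms could differ in new depression among them.

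**Conclusion.** The point holds as a contradiction about which outcome is primary, located in the analysis text itself. Taken literally, the economic comparison would use a non-primary outcome on which recovery is possible for only 600 of the 1800 definite cases.

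Its numerical effect is undetermined. On the planning rates the multiplier is about 2.25 to 3.4 when costs cover all definite cases or all screen-positives, and about 0.75 to 1.0 when costs and effects are both taken in depression cases. These figures assume equal arms, the plan's recovery rates, no arm difference in new depression (first range) and equal incremental cost per patient (second range). If the intervention is both better and cheaper, no multiplier applies. The documents do not show a fault in the QALY analysis, nor that its utility mapping is confined to depression.

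**What to change.** In the economic paragraph of Data management & analyses:

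1. Replace depression status with ICD-10 CMD status at 6 months as the clinical effect measure.
2. State the population, and take costs and effects from the same one as the primary clinical analysis. Trial objectives and outcomes and Sample size make that the definite cases. Table 2, however, marks the possible-cases outcome as primary and the definite-cases outcome as secondary, so this must be reconciled first.
3. Keep cost per depression recovery as a secondary analysis, with costs and effects both from depression cases.
4. Make the description of the utility measure consistent with CMD; the QALY method need not change.

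The cost is wording only. The CIS-R already provides both statuses, and no new data or change in sample size is needed. The change should be made before outcome data by arm are seen, so that the effect measure is not chosen with results in view.
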